# AIMS AND OBJECTIVES

We aim to assess the feasibility and acceptability of conducting an RCT to compare receiving ABC (an online-delivered, CBT, group-based, body image programme) alongside a psychoeducational body image booklet for women treated for breast cancer, with receiving the booklet only. Results will inform the design, management, and future delivery of an evaluation to assess effectiveness and cost-effectiveness in a definitive RCT.

Specific objectives are to:

- Establish appropriate, inclusive, and acceptable methods of participant recruitment, retention, and management procedures.
- Establish the feasibility and acceptability of quantitative data collection, including determining appropriate primary and secondary outcome measures.
- Adapt and test a measure of health and social care service use, to inform a future economic evaluation.
- Establish intervention adherence and acceptability (of online setting) among participants and ABC facilitators.

This study will examine uncertainties that need addressing before a definitive RCT:

- Recruitment processes and response rates: Responses from potential participants invited for randomisation and investigating reasons for declining.
- Intervention adherence and retention within the study: Percentage of participants completing each ABC session, reading the Macmillan booklet (in the control arm), and completing outcome measures at each assessment. This will additionally help calculate the sample size for the proposed follow-on RCT.
- Participants’ experience of randomisation to either the intervention or control arm and their experience of being in these arms.
- Participants’ responses and feedback to self-complete measures. This will determine suitability of the measures for an RCT.
- Adaptation and testing of a measure of health and social care service use: Assessment of comprehensiveness of the service use measure and acceptability of the measure to collect data for a health economic evaluation.

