The Leeds site does not have such follow-up appointments. Therefore, the clinical care team will review the medical records of their patients and identify women who have recently finished active treatment. To encourage diversity of participants, they will try to identify women across different ages and ethnicity. They will initially contact the individuals to ask if they are interested in finding out more about the study. If they are, and consent to have their contact details passed onto the research nurse (at the hospital), they will send out the SIL (Appendix 4), PIS (Appendix 2), EoIF (Appendix 4), and a pre-addressed, stamped envelope to the individual. Similarly, individuals interested in taking part in the study will be asked to either email, telephone, or return the EoIF to the research team. The research team will then contact the interested individual with further information about the study. For individuals who choose not to take part, the EoIF includes a question asking them to provide a brief reason why they made this decision. This may help inform the design and planning of a future definitive RCT.

To encourage greater diversity of participants, we will additionally advertise the study via various UK cancer support organisations, including Breast Cancer Now, Maggie’s, Keeping Abreast, and Flat Friends. This will hopefully capture women who are years beyond treatment and are no longer having contact with their hospital yet are struggling with BID. To engage women from underserved groups, we will also advertise the study via OUTpatients (supporting LGBTQIA+ individuals who have had cancer) and Black Women Rising (supporting women of colour who have had cancer). These organisations will advertise the study through their respective communication channels and social media platforms using a social media image (Appendix 5) like that of the poster, with Maggie’s displaying the physical posters (Appendix 3) in their centres. Interested women can either scan the QR code or enter the weblink which will take them to the PIS (Appendix 2) They can also telephone or email the research team (details on the poster) who can send them the PIS and EoIF.

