We will collect a variety of different type of data exploring acceptability and feasibility. This will inform the design of a future definitive RCT and help refine intervention, recruitment, and retention procedures. Figure 1 provides an outline of participant flow in the study and Table 1 provides an outline of the different assessments and their associated timepoints.

- - 1. **Quantitative measures of feasibility and acceptability**

We will collect the following quantitative data to assess feasibility and acceptability of the research design and ABC:

- - - 1. **Monitoring data**
- Rates of recruitment (and associated response rates), with attention to the method by which women were recruited and their demographic diversity.
- Rates of retention following randomisation:
  - Proportion completing ABC (number of sessions attended and between-session activities completed)
  - Proportion of control arm reading the Macmillan body image booklet (plus percentage of booklet read)
  - Proportion completing outcome measures at each assessment (plus data completeness rates; outcome measures described in 5.6.3).
    - 1. **Self-report rating scales included in outcome assessments (see 5.6.3)**
- Rating scales to explore acceptability of ABC (e.g., the group format, online nature, between-session activities; Appendix 9) - to be completed by ABC participants in the immediate post-intervention assessment, i.e., Week 9.
- A single rating scale examining how helpful participants found the ABC programme will also be included in the three- and six-month follow up assessments (see Appendix 31). This will allow monitoring of how participants’ perceptions of the programme and its impacts may develop over time.
- Rating scales to explore acceptability of the research process generally (e.g., information provided about the study, randomisation process, questionnaires; Appendix 10) – to be completed by all participants in the six-month post-intervention assessment i.e., Week 32.
  - 1. **Qualitative measures of feasibility and acceptability**

In addition to the above, we will collect the following qualitative data to assess feasibility and acceptability of the research design and ABC:

- - - 1. **Open-ended questions included in outcome assessments (see 5.6.3)**

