| **Interviews** | As appropriate | | | |

- - - 1. **Interviews**

Purposive sampling will be used to recruit a subset of 16-20 study participants to participate in semi-structured interviews. This approach will be used to explore the widest range of perspectives possible, ensuring that we have qualitative data from participants of different ages, ethnicities, sexual orientations, geographical locations, and socio-economic backgrounds.

These interviews will explore the experiences of participants from both conditions in relation to recruitment, randomisation, the Macmillan body image booklet, communication from the research team throughout the study, and completion of outcome measures. Participants from the intervention arm will also be asked about the acceptability of the ABC intervention.

We will target participants at different stages of the study and who may have had different experiences, which will enable us to identify barriers and solutions to participation and retention. This will include women who considered taking part at the beginning (i.e., they read the PIS) but decided not to proceed (Appendix 11), participants who dropped out immediately following randomisation (Appendix 12), participants who were randomised to the control arm but dropped out before the last questionnaire (see Appendix 13), participants who were randomised to the intervention arm but dropped out before the last questionnaire (see Appendix 14), participants who were randomised to the control arm and completed the whole study (i.e., completed the final assessment; Appendix 15), and participants who were randomised to the intervention arm and completed the whole study (i.e., completed the final assessment; see Appendix 16). We will endeavour to have an approximately equal number of participants reflecting each circumstance.

These interviews will occur across 12 months, with the sampling, data collection, and analysis happening concurrently and iteratively. All ABC facilitators will also be interviewed following intervention delivery to explore their experience of the programme, as well as their perceived barriers to participant retention, and solutions, if necessary.

- - 1. **Self-report validated outcome measures**

Data relating to self-report validated outcome measures will be collected to determine the suitability of these measures for use in a subsequent definitive RCT, rather than to draw conclusions about the relative efficacy of ABC.

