Participants will be asked to complete self-report outcome assessments at four timepoints:

- T1: Pre-intervention (i.e., baseline; Week 1)
- T2: Immediate post-intervention (within one week of finishing the last ABC session; Week 9)
- T3: Three-month post-intervention (Week 20)
- T4: Six-month post-intervention (Week 32).

However, the specific data that will be collected may differ at each timepoint. These will be clarified in the following sections.

As per the participant preferences, this assessment will be completed either online (via Qualtrics) or by paper (the participant will be sent the questionnaire and a pre-paid and addressed envelope to return).

- - - 1. **Demographics and cancer-related information**

We will collect contextual information about women participating in the study at pre-intervention (i.e., baseline; Week 1).

This will include information about their demographics (e.g., age, ethnicity, relationship status), as well as their cancer diagnosis and treatment (e.g., stage of cancer, time since finishing active treatment, modes of treatment received; Appendix 17).

Additional demographics questions will be included in the three-month follow up questionnaire to ensure that all relevant information is collected (see Appendix 32).

- - - 1. **Primary validated outcome measures**

The proposed primary outcome measures undergoing consideration for a subsequent RCT will be assessed at all four timepoints, and are as follows:

- Kessler Psychological Distress Scale (K10; Kessler et al., 2002; Appendix 18)

The K10 is a measure of non-specific psychological distress. Participants are asked to rate their emotional states on a 5-point scale over 10 items.

- Body Appreciation Scale-2 (BAS-2; Tylka & Wood-Barcalow, 2015; Appendix 19)

The BAS-2 is a measure of a person’s acceptance and/or favourable opinions towards their body. Participants are asked to rate each of the 13 items on a 5-point scale.

- Functional Assessment of Cancer Therapy – Breast (FACT-B Version 4): Breast Cancer Subscale (Brady et al., 1997; Appendix 20)

The FACT-B is a measure of health-related quality of life for breast cancer patients and includes five subscales. We will be using the Breast Cancer Subscale, whereby participants rate each of the 10 items on a 5-point scale.

- - - 1. **Secondary validated outcome measures**

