**Recruitment Avenue**

To help us understand how people found out about the study, can you please tell us which of the following applies to you (please select one option below)

- I was sent a letter or email from the NHS trust that treated me
  - Which NHS trust was this? ___________________
- I saw a poster in the waiting room of the NHS trust that treated me
  - Which NHS trust was this? ___________________
- I saw the study advertised via a cancer support organisation
  - Which organisation was this? (please select one option below)
    - Maggie’s
    - Flat Friends
    - Keeping Abreast
    - Breast Cancer Now
    - Live Through This
    - Other (please state) ____________________
      - How was the study advertised? (please select one option below)
        - Via a poster on the wall
        - Via an online forum
        - Via their social media
        - Via email
- I saw the study advertised on social media (**not** by the cancer support organisation)
  - Which social media platform was this? (please select one option below)
    - Instagram
    - Twitter
    - Facebook
    - Other (please state) ____________________
  - Who was the study advertised by? (please select one option below)
    - UWE Bristol
    - Centre for Appearance Research
    - Someone who has had breast cancer themselves and has a large following on social media
    - Other (please state) ____________________
- Other (please state) ____________________

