**12.32: Appendix 32: Additional Demographics Question**

How would you describe your sexual orientation? *For example: straight, lesbian, bisexual etc.*

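### Sexual orientation is asked only at Week 20 (T3), so it is never recorded for women who do not return that questionnaire

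*Protocol*

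**What the plan says.** The first listed objective, named as primary in the Trial Summary, is to "Establish appropriate, inclusive, and acceptable methods of participant recruitment, retention, and management procedures". Section 5.6.1.1 (Monitoring data) turns the recruitment part into an outcome: "Rates of recruitment (and associated response rates), with attention to the method by which women were recruited and their demographic diversity". Section 5.1 adds outreach to underserved groups: "we will also advertise the study via OUTpatients (supporting LGBTQIA+ individuals who have had cancer) and Black Women Rising". Section 5.6.2.2 (Interviews) plans purposive sampling of 16-20 participants, "ensuring that we have qualitative data from participants of different ages, ethnicities, sexual orientations, geographical locations, and socio-economic backgrounds".

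Section 5.6.3.1 collects demographics at baseline and then states: "Additional demographics questions will be included in the three-month follow up questionnaire to ensure that all relevant information is collected". Appendix 32 contains one question: "How would you describe your sexual orientation". Table 1 marks it at T3 only, with nothing at T1, T2 or T4. The amendment history (Appendix 30) shows that it was added in version 3, dated 24/10/24.

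The baseline form in Appendix 17 asks about age, region, gender identity (with trans and non-binary options), ethnic group, relationship status, employment and education, among other things. It does not ask about sexual orientation. Its list of recruiting organisations includes "Live Through This", which Appendix 23 identifies as the former name of OUTpatients. It has no option for Black Women Rising, but it does have a free-text 'Other' entry.

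**The concern.** A baseline characteristic first recorded at Week 20 is recorded only for women who are still responding at Week 20. Whether a woman has a value then depends on retention, which the study sets out to learn about. Any account of who was recruited by orientation describes T3 responders, and early loss by orientation cannot be seen.

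This matters because LGBTQIA+ women are a group the study deliberately tries to reach, and because orientation is a stated dimension for choosing interviewees. The women whose early departure would say most about barriers to taking part are the ones for whom the item is blank. No later analysis can recover an answer that was never requested.

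**Working it through.** The protocol states no figure on this point, so there is none to reproduce. The check sets the schedule against what the study wants to describe and then sizes the gap.

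**1. Who is asked.** Under section 5.4, consent and baseline data come before randomisation, so an item on the T1 form is put to all 120 randomised women. An item only on the T3 form is put only to those who complete T3. Table 1 has no second chance: a woman who misses T3 and returns T4 is still not asked.

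**2. Number without a value.** Missing = 120 × (proportion not returning T3). The protocol gives no T3 return rate, so a range is assumed:

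| Assumed non-return at T3 | Orientation missing, of 120 |
|---|---|
| 5% | 120 × 0.05 = 6 |
| 10% | 120 × 0.10 = 12 |
| 20% | 120 × 0.20 = 24 |
| 30% | 120 × 0.30 = 36 |

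The background section reports that 80% completed all assessment timepoints in the earlier in-person study. The complement, 20%, falls inside the range but is not itself a T3 loss rate. Women who return T3 and skip the item, which section 9 allows, would add to these counts.

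**3. Retention to T3 by orientation.** Orientation is known only if T3 is returned. Within any orientation group, the observed proportion returning T3 is (returned T3) / (returned T3) = 100%, whatever the true rate. It carries no information. Retention from T3 to T4 by orientation can still be estimated among T3 responders.

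**4. Recruited share by orientation.** Let a share p of the 120 belong to a minority-orientation group, with true T3 return r₁ in that group and r₂ in the rest. The share seen at T3 is

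p·r₁ / [p·r₁ + (1 − p)·r₂].

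Illustrative values (all assumed), with r₂ = 80%:

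| True share p | Seen if r₁ = 80% | Seen if r₁ = 60% |
|---|---|---|
| 3% | 3.0% | 2.3% |
| 5% | 5.0% | 3.8% |
| 10% | 10.0% | 7.7% |

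For the last row, 12 women × 0.60 = 7.2 and 108 × 0.80 = 86.4, so 7.2 / 93.6 = 7.7%. The share is undistorted if loss is equal across groups, but the data as scheduled cannot show whether it was.

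**5. Interview sampling.** Section 5.6.2.2 names six circumstances.
- Women who leave immediately after randomisation have no recorded orientation.
- Women in the two later drop-out categories have none if they left before T3. Those who leave between T3 and T4 have been asked, and so may some who stopped attending sessions but still return T3.
- Women who never consented complete no baseline form, so they lack every Appendix 17 item. The T3 timing is not the cause of that gap.
- The interview schedules for decliners and drop-outs (Appendices 11-14) do not ask about orientation.

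**6. What is unaffected.** Ethnic group and gender identity are on the T1 form, so recruitment and retention by either can use all randomised women as denominator.

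**The case against.** The strongest reply is that this is one descriptive variable, that no between-arm comparison depends on it, and that the protocol does not promise retention broken down by orientation. Section 5.6.1.1 attaches demographic diversity to recruitment, and the planned retention summaries are not split by demographics. That is right as far as it goes, and it limits the weight of the point. It does not remove it, because the recruitment description and the interview sampling are stated commitments and the first objective covers inclusive retention as well as recruitment.

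A second reply is that the item was added by amendment, apparently to make good an omission from the baseline form. The protocol does not say how many women had been enrolled by then, so the gain from moving it to T1 is unknown. This also stands. It is why the remedy has to cover women already in the study.

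A reader might infer more: that the study cannot tell whether it reached or kept any of its targeted groups, women of colour included, because Black Women Rising is absent from the route list. The documents do not support that. Ethnicity is recorded at baseline, and that route can be entered as free text and coded. OUTpatients is on the list under its old name, and gender identity is also asked at baseline. Nor are all women without a value drop-outs, since some may miss T3 and return T4.

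**Conclusion.** The point holds for sexual orientation before T3 and no further. As scheduled, orientation will be missing for every T3 non-responder: 6 to 36 of 120 on an assumed non-return of 5% to 30%. Three things follow by logic: the recruited share describes T3 responders only, loss before T3 by orientation cannot be assessed, and orientation cannot guide the selection of randomised women who leave before T3. How far the share is distorted depends on differential loss, which is unknown; 10% appearing as 7.7% is an illustration, not a forecast.

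The route list is a coding weakness and not a loss of measurement. No outcome comparison between arms is biased. This is a cheap improvement to a stated schedule, worth making because the missing information cannot be retrieved afterwards.

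**What to change.** - Ask the optional Appendix 32 item at T1 for women not yet enrolled.
- For women already enrolled, ask it at the next scheduled contact (T2, T3 or T4), or at withdrawal where consent allows.
- Ask it in the interviews with decliners and early leavers. This is the only way to obtain it for women who never consented.
- Report recruitment and retention by orientation with all randomised women as denominator and non-response shown as its own category.
- As a minor accompanying edit to Appendix 17, label the route as OUTpatients with its former name in brackets, and add Black Women Rising as an option.

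The cost is a questionnaire amendment, with matching changes to Table 1, section 5.6.3.1 and the affected interview schedules, and one more sensitive optional item at baseline. Women who have already left and cannot be contacted again will remain without a value, and the report should give their number.

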# INTERVENTION AND CONTROL

- 1. **ABC intervention**

ABC comprises seven 2-hour group sessions (with approximately 8 women per group) delivered online via Microsoft Teams and across 7 consecutive weeks. The intervention aims to improve body image among women treated for BC. Rooted in CBT, ABC uses strategies to alter unhelpful thoughts, reduce anxiety, and promote non-avoidant behaviours. Other topics are also explored, including sociocultural pressures for women, intimacy, physical activity, self-care, mindfulness, and relaxation. The sessions will be guided using PowerPoint slides, which will include text, images, and videos. Each session will include individual and group-based activities, and participants will be asked to complete between-session readings and activities. Table 2 provides an overview of ABC and its content.

Upon randomisation to the intervention arm, participants will be sent the Macmillan body image booklet (described in 6.3) and informed of the next available date to begin ABC. To prepare participants, they will be sent (via the post or email, as per the participant’s preference) a guide concerning session expectations (e.g., format, activities), in addition to clear instructions on how to use Microsoft Teams. Further, they will be sent all intervention materials. Any participants who do not have access to the internet (or have limited data use) will be provided with a data internet card.

A week prior to the first ABC session, participants will be asked to read the pre-session intervention materials (i.e., Session 1: Part 1) to help them start reflecting on their goals. In the session, there will be introductions and discussion of ground rules before the structured session content is delivered. All participants will be asked to have the second part of the intervention materials for the session (i.e., Session 1: Part 2) in front of them, to facilitate individual and group exercises. At the end, they will also be asked to complete two between-session activities at home (e.g., mirror exposure exercise) before the next session. They will also be advised to read the pre-session intervention materials (i.e., Session 2: Part 1) for the following week’s session. The same format will continue for all sessions (approximately 21 pages/session). This format (including intervention materials, between-session activities) has received positive feedback from study participants and PPI advisors.

Table 2: ABC content overview

| **Session** | **Content** |
| --- | --- |
| 1 | - Introduction to body image - Personal reflection upon the impact of body image concerns - Exploration of personal goals |
| 2 | - Introduction to the CBT approach - Physiological symptoms of anxiety - Exploration of body image and self-esteem - Relaxation training |
| 3 | - Stopping negative body-related self-talk - Developing alternative, balanced thoughts - Planning a self-care activity schedule - Relationship between body function and movement |
| 4 | - Sociocultural pressures for women in midlife - Internalisation of the youthful-thin ideal - Body comparisons – experimental activity - Body nurture with accepting self-talk |
| 5 | - Exploration of relationships and intimacy - Managing people’s reactions - Cognitive restructuring process - Physical activity and movement |
| 6 | - Identifying core beliefs - Modifying mistaken beliefs - Engaging the senses – mindful eating - Relaxation exercise |
| 7 | - Positive body affirmations - Reducing the chances of a setback - Dealing with a setback - Future plans |

- 1. **Intervention facilitators and fidelity**

Based on 60 women being in the intervention arm, and approximately 8 women per group, there will be approximately 6-8 ABC groups, running in both parallel and sequentially. Each group will be delivered jointly by two Cancer Support Specialist (CSS) (e.g. a Psychologist a nurse) from a Maggie’s centre. However, there will be a different pair of facilitators across each group, with some running only one group and others running up to three (depending on the capacity).

Working for a cancer support service, facilitators already have knowledge and skills to support people treated for breast cancer. Their expertise also complements one another, as the psychologist has undergone psychotherapeutic training (and thus can confidently deliver the CBT elements), whilst the CSS understands the treatment experience and impacts (e.g., on body functionality, intimacy), and thus can deliver the other intervention elements. All facilitators will receive two days of online training from the PI, who has considerable experience in training facilitators to deliver body image interventions (including ABC). They will be provided with materials and encouraged to make notes during the training to help support them during deliver of the ABC sessions.

Intervention fidelity will be assessed across different ABC groups and sessions. All ABC sessions will be recorded, and a selection (50%) will be assessed by the research team based on perceived competency (percentage reflecting how well facilitators delivered the sessions) and intervention adherence (percentage reflecting the extent to which facilitators completed each section of the sessions).

- 1. **Control arm**

Discussions with PPI advisors indicated that some form of body image-specific support should be provided for the control arm. Macmillan’s freely available psychoeducational body image booklet was considered appropriate, given that the thorough 77-page booklet provides a substantial amount of support and guidance relating to managing body image concerns. It explains the effects of cancer on body image, and provides practical guidance (e.g., make-up) and psychoeducational guidance (e.g., managing others’ reactions), in addition to some CBT strategies. Further, given that there is no current ‘treatment-as-usual’ in relation to body image support for women treated for breast cancer, this booklet may constitute the first time that these women have received support specifically relating to body image, and may even reduce distress. Upon randomisation to the control arm, participants will be sent the Macmillan body image booklet and encouraged to work through it gradually. The booklet can be accessed via the following webpage: <https://cdn.macmillan.org.uk/dfsmedia/1a6f23537f7f4519bb0cf14c45b2a629/791-source/body-image-mac14192>

1. **DATA ANALYSIS**
   1. **Primary aims**

The primary aims of the feasibility study will be delivered by conducting descriptive analyses of monitoring data (see 5.6.1.1) and self-report rating scales (see 5.6.1.2), as well as qualitative analyses of open-ended questions (see 5.6.2.1) and interviews (see 5.6.2.2). This will help indicate feasibility and acceptability of the whole research process and the intervention, which will help inform a definitive RCT.

- - 1. **Analysis of quantitative data**
       1. **Monitoring data**

Descriptive analyses (i.e., percentages and confidence intervals) will be conducted on numbers relating to recruitment (including numbers of eligible women who decide not to proceed after reading the PIS) and retention following randomisation, including numbers who complete ABC (i.e., number of sessions attended and between-session activities completed), who read the Macmillan body image booklet (in the control arm; including percentage of booklet read), and who complete self-report outcome measures at each assessment timepoint (including data completeness rates). We will assess the extent of missing data, withdrawals and loss-to-follow-up.

We will report data in line with the Consolidated Standards of Reporting Trials (CONSORT) 2010 Statement showing attrition rates and loss to follow-up.

- - - 1. **Self-report rating scales**

Descriptive analyses (i.e., means, standard deviations, percentages) will be conducted on the ratings scales related to acceptability of ABC (e.g., the group format, online nature, between-session activities; Appendix 9), as well as those related to acceptability of the research process generally (e.g., information provided about the study, randomisation process, questionnaires; Appendix 10).

- - 1. **Analysis of qualitative data**
       1. **Open-ended questions**

The responses to the open-ended questions asking for feedback on ABC (e.g., the group format, online nature, between-session activities; Appendix 9) and the research process generally (e.g., information provided about the study, randomisation process, questionnaires’ Appendix 10) will be analysed in NVivo using thematic analysis (Braun & Clarke 2006). The analytic process of ‘codebook’ thematic analysis will be used (Braun & Clarke 2006, 2022), whereby text will be coded using a priori codes and themes relating to feasibility and acceptability (informed by O’Cathain et al 2015).

- - - 1. **Interviews**

Interviews will be digitally recorded, transcribed verbatim, and analysed in NVivo using thematic analysis (Braun & Clarke 2006). The analytic process of ‘codebook’ thematic analysis will be used (Braun & Clarke 2006, 2022), whereby transcripts will be coded using a priori codes and themes relating to feasibility and acceptability (informed by O’Cathain et al 2015).

- 1. **Analysis of self-report outcome measures**

The self-report outcome measures (K10, BAS-2, FACT-B: Breast Cancer Subscale, Hopwood Body Image Scale, and BREAST-Q: Sexual Well-Being Scale) are each well-established validated measures which will be scored according to the most appropriate guidelines. The design (pre- post- two arm parallel randomised controlled trial) and the selected measures are amenable to analysis using long-established statistical techniques. The analysis will proceed using the intention-to-treat analysis set with the statistician blinded to allocation. These analyses include:

- Descriptive statistics (including mean and standard deviation) by randomised arm at each time point (T1, T2, T3, and T4).
- Unadjusted statistical comparison between arms at each timepoint (T1, T2, T3, and T4) using the independent samples *t*-test with 95% and 80% confidence intervals and quantification of effect size using Cohen’s *d*. If statistical assumptions do not seem tenable, robust non-parametric bootstrap equivalent tests will be used.
- Adjusted statistical comparison between arms at each timepoint (T2, T3, T4) will be conducted controlling for commensurate baseline measures using ANCOVA (Analysis of Covariance) along with 95% and 80% covariate adjusted confidence intervals and quantification of effect size using partial eta -squared. If statistical assumptions do not seem tenable, robust remedies will be considered, including a baseline by randomised arm interaction effect, or homoscedasticity corrected robust standard errors (HC3) or the robust non-parametric bootstrap equivalent ANCOVA.
  1. **Heath economic evaluation**

The draft ABC AD-SUS (Appendices 23-25) will undergo testing for the following:

- Acceptability: This will be assessed via the proportion of participants completing the measure, percentage of missing items, and consideration of the clarity of any questions associated with missing data.
- Comprehensiveness: This will be assessed via open-ended questions included in the AD-SUS asking participants to report any ‘other’ services not reported elsewhere in the measure (missing items).
- Redundancy: This will be assessed through consideration of any service items included in the AD-SUS but not reported as being used by any participant (redundant items).

These results, plus feedback from participants, will inform a final version of the AD-SUS for a future definitive trial.

Acceptability of the EQ-5D-5L (Appendix 26), ReQoL-10 (Appendix 27), and WSAS (Appendix 28) will be assessed using completion rates (proportion of participants completing each of the measures and percentage of missing items within each of the measures), plus feedback from participants. Service use, health-related quality of life and the WSAS will be summarised and reported descriptively.

